**Fig. 1 Fig1:**
[figure not shown]
Cluster-randomised trial intervention scheme

### Study setting

The study population will be AP professionals who work in the SNS, assigned to 6 TU (total *N* = 802, Córdoba = 256, Almería = 147, Jaen = 185, Burgos = 64, Ponferrada = 63, and Zaragoza Sector I = 87), whether AP tutors (*N* = 297) or residents (*N* = 595) of Family and Community Medicine and Nursing.

### Eligibility criteria

-Inclusion criteria: AP professionals who are active and give their informed consent to participate in the study.

-Exclusion criteria: Having previously attended a mindfulness training course or workshop of at least 4 weeks, being an active mindfulness practitioner, being on prolonged sick leave during fieldwork, or having mental disorders discouraging the intervention.

### Intervention scheme

The interventions will be based on the MBSR programme [8–10] designed by Jon Kabat-Zinn and used at the Medical Center of the University of Massachusetts. Certain self-compassion practices of the Mindful Self-Compassion (MSC) programme [17–19] (Table 1) will be incorporated. The programmes to be tested will be adapted to the participating health care group and will differ by their duration and time dedicated to the tasks [30]:Standard program: The format will be 8 weekly sessions of 2.5 h each. Participants must practice at home for 30 min a day.Abbreviated program: The format will be 4 weekly sessions of 2.5 h each. Participants must practice at home for 15 min a day.

**Table 1 Tab1:** Mindfulness and self-compassion training programs

	8-WEEK PROGRAM	4-WEEK PROGRAM
PRESENTATION BASELINE MEASUREMENT	General explanation, objectives, schedule. Pre-intervention measurements: general data, FFMQ, SCS, PSQ, MBI-GS, JSPE, GADS, AES questionnaires.	
1st SESSION	Raisin exercise. What is mindfulness? Practice: body scan. Informal practice: brushing.teeth Task: 30′ body scan.	Raisin exercise. What is mindfulness? Managing thoughts and emotions during practice. Practice: body scan. Informal practice: brushing.teeth Task: 30′ body scan.
2nd SESSION	Concepts: stress and burnout Practice: mindful breathing (sitting). 3-min mindfulness practice. Informal practice: mindful shower, 3′. Task: 30′ body scan + 10′ sitting.	Concepts: stress and burnout. Primary and secondary suffering. Practice: mindful breathing (sitting). 3-min mindfulness practice. Informal practice: mindful shower, 3′. Task: 30′ body scan + 10′ sitting.
3rd SESSION	Posture. Being versus doing. Managing thoughts and emotions during practice. Practice: yoga (standing meditation). Informal practice: washing the dishes, 3′. Task: alternating body scan or yoga + 15′ sitting.	Unconditional love (metta). Compassion. Practice: conscious movements. Metta for oneself and for others. Informal practice: washing the dishes, 3′, thank you letter. Task: alternating body scan or yoga + 15′ sitting.
4th SESSION	Attention. Primary and secondary suffering. Practice: yoga (sitting meditation). Practice: making the bed, 3′. Task: alternating body scan or yoga + 15′ sitting.	Positive psychology. Values. Practice: walking meditation. The funeral. Informal practice: the first bite, 3′, 3 positive things. Course feedback. Incorporating mindfulness into daily life. Course evaluation and satisfaction questionnaire. Repeating the questionnaires.
5th SESSION	Time management. Problem resolution. Practice: walking meditation. Practice: the first bite. Task: yoga alternating with 30′ sitting. Start walking meditation.	
6th SESSION	Unconditional love (metta). Compassion. Practice: Metta for oneself and for others. Informal practice: thank you letter. Task: yoga alternating with 30′ sitting + walking meditation.	
7th SESSION	Positive psychology. Values. Practice: a compassionate gesture, safe place. The funeral. Informal practice: 3 positive things, 3′. Task: 45′ method of choice.	
8th SESSION	Course feedback. Practice: review course practices. Incorporating mindfulness into daily life. Course evaluation and satisfaction questionnaire.	
POST-INTERVENTION MEASUREMENT	Repeat the questionnaires.	Repeat the questionnaires.
REEVALUATION (3 MONTHS)	Repeat the questionnaires.	Repeat the questionnaires.

The sessions are held in groups, alternating moments of silence with others of collective exploration on the best strategies to address complex and difficult situations, always looking for practical applications in the personal and professional fields. The contents of the sessions are oriented to the knowledge of mindfulness, the perception of reality, the power of emotions, the reaction to stress and emotional tension, resilience, responding to stress, using mindful communication, taking care of oneself, time management, and integrating mindfulness into everyday life.

The training programmes will be unified in the different TU and taught by the same two instructors throughout the course to avoid any variability associated with the therapist. The instructors will have proven skills through university accreditation to deliver this training and will carefully follow the interventions, using standardised and uniform methodological criteria, which will be stated in a manual.

3) CG: without intervention. Participants will only receive a 1-h information session explaining the study design and their role in the study and inviting them to complete the expected data at two time points (coinciding with the interventions in the EG8). They will pledge not to receive any intervention and will be asked not to participate in the practice of any session of full attention or meditation techniques during the study period. After the fieldwork, they will be offered the opportunity to participate in the abbreviated training programme.

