**Methods:**

The MINDUDD study is a multicentre cluster randomised controlled trial with three parallel arms. Six Teaching Units will be randomised to one of the three study groups: 1) Experimental Group-8 (EG8); 2) Experimental Group-4 (EG4) Control group (CG). At least 132 subjects will participate (66 tutors/66 residents), 44 in the EG8, 44 in the EG4, and 44 in the CG. Interventions will be based on the Mindfulness-Based Stress Reduction (MBSR) program, including some self-compassion practices of the Mindful Self-Compassion (MSC) programme. The EG8 intervention will be implemented during 8 weekly face-to-face sessions of 2.5 h each, while the EG4 intervention will consist of 4 sessions of 2.5 h each. The participants will have to practice at home for 30 min/day in the EG8 and 15 min/day in the EG4. The Five Facet Mindfulness Questionnaire (FFMQ), Self-Compassion Scale (SCS), Perceived Stress Questionnaire (PSQ), Maslach Burnout Inventory (MBI), Jefferson Scale of Physician Empathy (JSPE), and Goldberg Anxiety-Depression Scale (GADS) will be administered. Measurements will be taken at baseline, at the end of the programs, and at three months after completion. The effect of the interventions will be evaluated by bivariate and multivariate analyses (Multiple Linear Regression).

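### Home practice is set at 15 min/day (EG4) and 30 min/day (EG8) in the text, but Table 1 gives both arms the same tasks after sessions 1 to 3

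*Protocol article*

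**What the plan says.** The abstract (Methods) states the home-practice requirement for both experimental arms: "The participants will have to practice at home for 30 min/day in the EG8 and 15 min/day in the EG4".

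The section Intervention scheme repeats it arm by arm. For the standard programme: "Participants must practice at home for 30 min a day". For the abbreviated programme: "Participants must practice at home for 15 min a day". The same section says that the programmes "will differ by their duration and time dedicated to the tasks", so practice time is a declared part of the contrast.

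Table 1, in the same section, lists a home task after most sessions:

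- **Session 1, both columns:** "Informal practice: brushing.teeth Task: 30′ body scan".
- **Session 2, both columns:** "Task: 30′ body scan + 10′ sitting".
- **Session 3, both columns:** body scan alternated with yoga, plus 15 minutes of sitting. No length is given for the body scan or the yoga.
- **Session 4:** no home task in the EG4 column. EG8 has further tasks after sessions 4 to 7.
- **Session 7, EG8:** "Task: 45′ method of choice".

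The table does not say how often each task is to be done.

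**The concern.** EG4 against EG8 is the comparison that the hypothesis turns on: whether the shorter programme does no worse than the standard one. The article describes the shorter programme as lighter in two ways, with fewer sessions and less daily practice at home. Table 1 supports the first and contradicts the second for every week in which EG4 has a home task.

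At stake is what a favourable EG4 result would mean. If participants are given the Table 1 tasks, such a result could not be attributed to a programme with half the daily practice, because the prescribed practice would have been the same in both arms over those weeks. If participants are given the times in the text, the published table misdescribes the programme for anyone who wants to adopt it. The practice journal is affected too. A participant in EG4 who does 15 minutes of body scan in week 1 meets the text but falls short of the table.

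**Working it through.** **Inputs.** Text: 15 min/day (EG4) and 30 min/day (EG8), from the abstract and Intervention scheme. Table 1: 30 min after session 1 and 30 + 10 = 40 min after session 2 in both arms; 45 min after session 7 in EG8. Sessions are weekly, so EG4 has three between-session weeks (21 days).

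**Step 1: the stated times against the table.**

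| Task set after | Table 1, EG4 | Text, EG4 | Table 1, EG8 | Text, EG8 |
|---|---|---|---|---|
| Session 1 | 30 min | 15 min/day | 30 min | 30 min/day |
| Session 2 | 40 min | 15 min/day | 40 min | 30 min/day |
| Session 3 | 15 min sitting + body scan or yoga (total not stated) | 15 min/day | same as EG4 | 30 min/day |
| Session 4 | no task | – | further task | 30 min/day |
| Session 7 | – | – | 45 min | 30 min/day |

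The 15 min/day cannot be reproduced from the EG4 column. The 30 min/day for EG8 matches the task after session 1 but not those after sessions 2 and 7.

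**Step 2: totals, if the tasks are daily (an assumption).**

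- Table 1, EG4, weeks 1 and 2: 30 × 7 + 40 × 7 = 210 + 280 = 490 min.
- Text, EG4, three between-session weeks: 15 × 21 = 315 min.
- Text, EG4, if a full four weeks were counted: 15 × 28 = 420 min, still below 490.

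**Step 3: adding week 3, as a range.** Assume the body scan stays at 30 min and yoga lasts between 0 and 30 min. The alternating task then averages (30 + yoga)/2 + 15.

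- Yoga 0 min: (30 + 0)/2 + 15 = 30 min. Three-week total: (30 + 40 + 30) × 7 = 700 min.
- Yoga 30 min: (30 + 30)/2 + 15 = 45 min. Three-week total: (30 + 40 + 45) × 7 = 805 min.
- Against the text: 700/315 = 2.2 and 805/315 = 2.6.

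**Step 4: the difference between arms in weeks 1 to 3.** By the text, 30 − 15 = 15 min/day. By Table 1 it is 0, because the printed tasks are the same. The zero does not depend on the yoga length or on how often the tasks are done, provided the frequency is the same in both arms.

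**Step 5: could frequency reconcile the two?** The days per week at which a task averages the stated daily time are (stated minutes × 7)/task minutes.

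- EG4: 15 × 7/30 = 3.5 days for the first task; 15 × 7/40 = 2.6 days for the second.
- EG8: 30 × 7/30 = 7 days for the first; 30 × 7/40 = 5.25 days for the second.

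The same printed task would have to be done half as often in EG4 as in EG8. Nothing in the article says so.

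**The case against.** Several counter-arguments have force, and they limit the point.

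- **The main contrast is intact.** Four versus eight sessions of 2.5 h (10 h versus 20 h of teaching) is stated consistently, and the objective defines the programmes by number of sessions. This stands. Only the home-practice component is contradictory, and the overlap covers weeks 1 to 3.
- **No planned analysis uses practice minutes.** The per-protocol set is defined by sessions attended (6 of 8, or 3 of 4). The journal records whether exercises were done, not minutes against a target. The sample size rests on the FFMQ. This also stands: no analysis set or sample-size figure changes.
- **Table 1 states no frequency.** This is true, so the minute totals are conditional. But the text's requirement is per day, and identical tasks in both columns still leave the declared difference unexplained.
- **An article condenses, and the manual may settle it.** The manual is not shown and may already give one clear figure. But the finding is not about missing detail: the article prints two specifications that cannot both hold.

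Two stronger readings are tempting. A reader might infer that different Teaching Units could receive different versions. The documents point the other way: the programmes are to be unified across units and taught by the same two instructors from a manual, with some sessions audio-recorded and checked by external experts. A reader might also infer that the manual is wrong. Nothing in the article shows what the manual says.

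**Conclusion.** The contradiction is on the face of the article and needs no outside source. The text requires half as much daily practice in EG4 as in EG8; Table 1 sets the same tasks in both arms after sessions 1, 2 and 3, which are all the home tasks that EG4 has. Without any assumption about frequency, the EG4 tasks of 30 and 40 minutes exceed 15, and the EG8 tasks of 40 and 45 minutes exceed 30.

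If the tasks are daily, EG4 receives 490 minutes in two weeks, against 315 by the text over three. With week 3 included, the table gives 2.2 to 2.6 times the text, on the assumption of a 30-minute body scan and 0 to 30 minutes of yoga.

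The consequence is for interpretation, not for sample size or analysis sets: as printed, the article does not settle whether EG4 versus EG8 tests fewer sessions with less daily practice, or fewer sessions with the same weekly tasks while the programme runs. It should be corrected. The review takes no position on which practice time is right.

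**What to change.** Reconcile the abstract, the two programme descriptions in Intervention scheme, and both columns of Table 1, session by session. State one home-practice specification per arm and week, including how often each task is done and the length of the session 3 task. Check the instructor manual and the practice journal against it and align them where they differ. Then describe the EG4 versus EG8 comparison in the same terms, so that readers know whether daily practice is part of the contrast. Which figures apply is for the intervention team to decide.

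The cost is an edit to the text or the table, with any matching edit to the manual and journal. Sample size, randomisation and the planned analyses are unaffected. The reconciliation should be done before the programmes are delivered; if delivery has begun, the report should state which specification participants were actually given.

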### Outcomes and measures

The professionals will be asked to complete pre- and post-intervention questionnaires. The pre-intervention questionnaire will be filled out upon recruitment (baseline). The post-intervention questionnaire will be completed at 4 (EG4) or 8 weeks (EG8 and CG) after baseline and at 3 months after completion.

To measure the dependent variables or outcomes, the following instruments will be used (an additional file shows this in more detail [see Additional file 1]):

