## Methods/design

### Study design (Fig. 1)

The MINDUUDD study comprises an open-label, pragmatic, non-inferiority, multicentre, cluster randomised controlled trial with three parallel arms. The participating UUDDs will be randomised to one of the three study groups. Interventions will last for 8 weeks for one group (EG8) and 4 weeks (EG4) for the other. In both groups, there will be a follow-up at three months to check the maintenance of the programs’ effect. The control group (CG) will be reassessed 8 weeks after the start of the fieldwork.

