### Data collection and data management

The measurements will be taken at three time points: 1) Pre-intervention (initial or baseline; one week before the interventions begin, participants from all groups will be invited to a face-to-face meeting); 2) Post-intervention (final, one month for EG4 and two months for EG8, and simultaneously with the latter for CG participants); and 3) Three months after the interventions, at which time participants of EG4 and EG8 will be reconvened for a face-to-face session.

To measure adherence to the training programs, the sessions attended by the participants will be continuously monitored and followed up, and students must write in a personal notebook or journal whether they did the exercises at home and show it to the instructor in each session for supervision.

The data obtained (data collection notebook and questionnaires) will be collected and sent to the coordinating headquarters for further processing, debugging, and statistical analysis. Double data entry will be used for all questionnaires to keep the rate of data errors very low.

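### EG4 and the control group share no measurement time after baseline, and the control group has no 3-month measurement, so the EG4-control contrast carries any time trend and a lasting effect against no intervention cannot be shown

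*Protocol article*

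**What the plan says.** **First post-baseline measurement.** Outcomes and measures states: "The post-intervention questionnaire will be completed at 4 (EG4) or 8 weeks (EG8 and CG) after baseline and at 3 months after completion". Data collection and data management gives the same timing: "final, one month for EG4 and two months for EG8, and simultaneously with the latter for CG participants".

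**Control group.** Study design says: "The control group (CG) will be reassessed 8 weeks after the start of the fieldwork". Intervention scheme describes the control participants' role as "inviting them to complete the expected data at two time points (coinciding with the interventions in the EG8", and adds: "After the fieldwork, they will be offered the opportunity to participate in the abbreviated training programme".

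**Three-month follow-up.** Study design, having just named the two intervention groups, says: "In both groups, there will be a follow-up at three months to check the maintenance of the programs’ effect". Data collection and data management describes the third measurement as "Three months after the interventions, at which time participants of EG4 and EG8 will be reconvened for a face-to-face session". Table 1 lists the 3-month re-evaluation for the 8-week and 4-week programmes only.

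**Use of the data.** Sample size is based on a difference of 15 FFMQ points between each experimental group and CG. Statistical methods compares pre-post differences between the groups by repeated-measures ANOVA, followed by a multilevel regression. Two sections (Quality controls, monitoring and follow-up; Strengths and limitations) give the third measurement the purpose of showing that the programmes' effect persists.

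**The concern.** A control arm is there to show what would have happened over the same period without the programme. For EG4 it does not do this. EG4's pre-post difference covers four weeks and CG's covers eight, so whatever moves scores in everyone between weeks 4 and 8 is counted as part of the EG4 effect, with its sign reversed.

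The article gives some reason to expect change over time. Background ties residents' work stress to emergency shifts, and Strengths and limitations notes that some participants finish their training soon after the study.

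At three months there is no untreated comparator at all. Scores that stay above baseline in EG4 and EG8 could reflect a lasting programme effect, a general trend or regression to the mean. This is fixed by the data collection schedule. No later analysis plan can recover a control score that was never collected.

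**Working it through.** **1. Does CG have a 3-month measurement?** Read alone, the sentence in Outcomes and measures could be taken to give one. Four other places point the other way: CG completes data at two time points (Intervention scheme); its one reassessment is at 8 weeks (Study design); only EG4 and EG8 are reconvened (Data collection and data management); and Table 1 has no control column. CG also has no programme from which three months after completion could be counted. The reading that fits all of these is that CG has none.

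**2. Weeks since baseline by arm**, taking 3 months as 13 weeks (my convention):

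| Measurement | EG4 | EG8 | CG |
|---|---|---|---|
| Post-intervention | 4 | 8 | 8 |
| Follow-up | 4 + 13 = 17 | 8 + 13 = 21 | none |

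Data collection places baseline one week before the programmes start. Counting from programme start instead shifts all arms alike and leaves the 4-week gap unchanged.

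**3. What each contrast estimates.** Let D4 be the change by week 4 that would occur in any arm without a programme, D4 + d the same change by week 8, and E4 and E8 the programme effects at the end of each programme.

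- EG8 − CG = (E8 + D4 + d) − (D4 + d) = E8. No bias.
- EG4 − CG = (E4 + D4) − (D4 + d) = E4 − d. The full drift d enters.
- EG4 − EG8 = E4 − E8 − d. The drift term is present here too, but time since completion is matched (see the objection).

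If untreated FFMQ scores rise over weeks 4 to 8, EG4's benefit over CG is understated. If they fall, it is overstated.

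**4. The plan's own target, reproduced.** With a 15-point difference, SD 20, two-sided alpha 0.05 and power 0.80: n = 2 × [20 × (1.960 + 0.842) / 15]² = 27.9, so 28 per group. Allowing for 25% loss, 28 / 0.75 = 37.3, so 38, as stated. The 15 points is therefore the right yardstick for the bias, and the finding does not otherwise depend on this calculation.

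**5. Illustrative size.** The document gives no drift, so the weekly values below are assumptions. Bias = 4 weeks × drift per week, ignoring sign. The last two columns give the two-sided false-positive rate for EG4 versus CG if E4 = 0, with 44 per arm and SD 20: SE = 20 × √(2/44) = 4.26 ignoring clustering, or 20 × √(2 × 2.05/44) = 6.11 with design effect 1 + (22 − 1) × 0.05 = 2.05.

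| Drift per week | Bias (points) | Share of 15 | False-positive rate, no clustering | False-positive rate, design effect 2.05 |
|---|---|---|---|---|
| 0 | 0 | 0% | 5% | 5% |
| 0.25 | 1 | 7% | 6% | 5% |
| 0.5 | 2 | 13% | 8% | 6% |
| 1 | 4 | 27% | 16% | 10% |
| 2 | 8 | 53% | 47% | 26% |

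With a common measurement time for EG4 and CG, the gap and the drift term are both zero.

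**The case against.** The strongest reply concerns EG4 versus EG8. The stated hypothesis compares the two programmes, and with programmes of unequal length one cannot match both elapsed time and time since completion. Measuring each arm when its programme ends, and again three months later, matches time since completion. That is a legitimate choice, and it stands. Making week 8 the main EG4-EG8 contrast would compare EG4 four weeks after its last session with EG8 at its last session, swapping one imbalance for another.

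Three further objections also stand:

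- At three months both randomised programme arms are measured, so durability does not rest on within-arm change alone. A randomised EG4-EG8 comparison remains.
- Repeated questionnaire completion does not explain a difference at the first post-baseline visit, because by then every arm has completed the set once before.
- The drift values are arbitrary inputs. The article's remark about emergency shifts concerns stress in residents, who are half the planned sample (66 of 132), and says nothing on FFMQ drift or its direction.

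None of this answers the EG4-CG contrast. CG has no programme, so matching on time since completion cannot justify measuring it four weeks later than EG4. Strengths and limitations explains why follow-up is not longer, but not why CG is left out of it.

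**Conclusion.** The point holds in two specific places. First, EG4 and CG have no common time after baseline, so any common change over weeks 4 to 8 passes in full into a contrast on which the sample size is built. Second, the 3-month data contain no untreated comparator. They can compare EG4 with EG8 and describe maintenance within each arm, but cannot establish an effect that lasts relative to no intervention.

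The size of the first problem is unknown. It is zero without drift, and 1 to 8 FFMQ points (7% to 53% of the target) under the assumed 0.25 to 2 points per week, in either direction. The false-positive rates are equally illustrative: they assume SD 20, no loss of participants and, where used, an ICC of 0.05.

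A reader might infer that study arm is confounded with elapsed time throughout the trial, or that the main programme comparison is invalid. The documents do not support that. EG8 versus CG is aligned at week 8, and EG4 versus EG8 is matched on time since completion at both visits.

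**What to change.** 1. Keep the end-of-programme and 3-month measurements as they are for EG4 versus EG8.
2. Give EG4 and CG a common time point. Either CG completes the questionnaires at week 4 and that measurement is used for the EG4-CG contrast, or EG4 completes them at week 8 and that comparison is named as a sensitivity check. The week-4 control questionnaire is the cleaner option for this contrast: it leaves EG4's schedule untouched and both arms are then answering for the second time.
3. Have CG complete the questionnaires at the 3-month follow-up, before its training offer, and report 3-month effects as differences from CG. State the date: EG4's visit falls at about week 17 and EG8's at about week 21, so a single control round matches only one of them exactly.
4. If CG is not measured at three months, limit the durability conclusion to EG4 versus EG8 and within-arm maintenance, and say so under Strengths and limitations.

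The cost is one or two extra questionnaire rounds in groups of 44 (a further one if CG is to match both 3-month dates), with allocation, programmes and sample size unchanged. The downsides are added burden, possible extra control dropout, and perhaps a longer period in which CG is asked to avoid meditation and waits for training. Training is already offered only after the fieldwork, but the article does not date its end, so the length of any extra wait cannot be stated.
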